### Washout Period and Concomitant Treatments

No formal washout period was required before enrollment. To minimize potential confounding, all concomitant treatments used before enrollment, including physical therapy and medications, were comprehensively documented at baseline. During this trial period, participants were required to discontinue any additional therapies that could interfere with outcome assessment immediately, as specified in the inclusion criteria.

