### Participants Recruitment

This study used a randomized controlled, single-blind trial method, with participants recruited from the outpatient departments of Shanghai Municipal Hospital of TCM. A total of 100 patients were randomly assigned to an observation group (TNO) and a control group (TNM), with 50 patients in each group (Textbox 1).

Textbox 1.Inclusion and exclusion criteria.Inclusion criteriaMeeting the diagnostic criteria for the nonspecific low back pain set by the North American Spine Society and Chinese expert consensus [30,31].Being between the ages of 20 and 59 years.During the trial period of the research method, immediately stopping any therapies that may affect the determination of research effectiveness.Participating in this study, cooperating with the doctor’s arrangements, and signing an informed consent form.Exclusion criteriaExcluding specific low back pain lesions such as lumbar disc herniation and lumbar spondylolisthesis, and those related to bone joints and the spinal canal.Being patients with severe heart, lung, liver, and kidney diseases.Being individuals undergoing other clinical trials.Being individuals with a history of spinal surgery, spinal injury or deformity, or fracture.Being patients with combined acute infections, cancer, rheumatic and immune diseases, and mental illnesses.Being individuals with other primary functional disorders.

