### Dropout Criteria

The exclusion criteria were (1) not persisting in treatment or not following the treatment plan, (2) voluntarily requesting withdrawal, (3) having other serious concurrent diseases during the treatment process, and (4) using other treatment methods in combination.

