#### Infrared Thermal Imaging

Using infrared thermal imaging (FLIR ONE Pro, FLIR Systems, Inc) measurement method: maintain indoor temperature at 26 ℃±2 ℃, humidity at 45%-60%, maintain stable indoor air without convection, and avoid direct wind blowing to the examination site or between the subject and the camera. The subject shall not take any medication that affects body temperature orally within 24 hours, shall not undergo physical therapy, and shall not drink alcohol. The subject should lie prone, rest for a moment, maintain a certain balance in body temperature, wait for the skin to dry and become sweat-free, and then expose the tested area for 5 minutes before taking photos. The corresponding colors on the infrared image from high temperature to low temperature are white, deep red, red, light red, yellow, green, light green, light blue, deep blue, and black. Identify the pain points in the patient’s area and mark them accordingly. Measure the temperature of the pain points in the pain area before enrollment, at week 1, at week 2, and after week 4 of treatment. The location of the pain points in the pain area is determined based on palpation, patient feedback, and the first infrared thermography image. A low temperature in the pain area before treatment indicates poor local blood circulation and a decreased pain threshold. A high temperature at pain points after treatment indicates good local blood circulation and an increased pain threshold. The testing unit we used was ℃.

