To control multiplicity, a hierarchical testing strategy will be applied. The primary end point (change in VAS from baseline to wk 4) will be tested at a 2-sided α level of .05. Secondary outcomes (JOA score, tenderness score, muscle tension, and infrared thermography) will be tested sequentially only if the preceding end point reaches statistical significance, thereby controlling the family-wise error rate. Longitudinal group-by-time interactions across all postbaseline time points will be considered exploratory.

Clinically meaningful improvement will be evaluated using responder analyses in addition to continuous outcomes. A reduction of ≥2 points on the VAS and an improvement of ≥4 points on the JOA score will be defined a priori as the minimal clinically significant difference. The proportions of responders will be compared between groups using generalized estimating equations, with effect sizes reported as risk ratios and 95% CIs.

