#### Analysis of the Primary Outcome

The primary outcomes will be evaluated at baseline, intervention 1 week, 2 weeks, 4 weeks, and follow-up. We will conduct a sensitivity analysis on missing data (intention-to-treat analysis). The primary end point is the average change in the VAS scale from baseline to week 4 (primary end point) and week 8 (durability assessment). The baseline covariates include height, gender, age, cardiovascular history, and weight. The entire outcome scale will be measured at baseline. When the distribution is normal, nonpaired *t* tests are used to compare 2 groups, and 1-way ANOVA and repeated measures ANOVA are used to compare multiple groups. Sensitivity analysis using multiple input techniques (chain equation inputs) will be included to evaluate the impact of missing data on the main results. In addition, we will compare participants randomly assigned to the TNO and TNW groups, who received treatment considered to have high fidelity allocation. The percentage of missing data is 20%, and 5 input datasets will be used for analysis, which is the recommended minimum quantity. Before conducting any analysis, investigate any missing data patterns, identify the reasons for the missing data, and investigate the patterns to determine the validity of the hypothesis.

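### Prior treatment is recorded to limit confounding but no stated analysis uses it, which costs precision and blurs the responder results without biasing the primary comparison

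*Protocol article*

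**What the plan says.** All of the following is in the protocol article.

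- **Washout Period and Concomitant Treatments:** "No formal washout period was required before enrollment". To limit confounding, "all concomitant treatments used before enrollment, including physical therapy and medications, were comprehensively documented at baseline". During the trial, "participants were required to discontinue any additional therapies that could interfere with outcome assessment immediately".
- **Participants Recruitment (Textbox 1):** an inclusion criterion asks for "immediately stopping any therapies that may affect the determination of research effectiveness". It applies to every participant, whatever the arm.
- **Dropout Criteria:** one criterion is "using other treatment methods in combination".
- **Randomization and Allocation Concealment:** a random number table in order of enrollment. No stratification factor is described.
- **Statistical Analysis:** the mixed model has group, categorical time, their interaction and a random intercept, with baseline as one of the five repeated measurements. The primary estimand is the between-group difference in VAS change from baseline to week 4. For responders, "A reduction of ≥2 points on the VAS and an improvement of ≥4 points on the JOA score will be defined a priori", and groups are compared by risk ratios from generalized estimating equations.
- **Analysis of the Primary Outcome:** "The baseline covariates include height, gender, age, cardiovascular history, and weight".

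On timing, muscle tension, tenderness and thermography are first measured before enrollment. For VAS and JOA the article says only that the first reading is at baseline and precedes the intervention.

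**The concern.** Recording a variable does not adjust for it. The article names the record of earlier treatment as its safeguard, then sets out a model and a covariate list that leave it out, while height, weight and cardiovascular history are included.

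Suppose a patient's baseline VAS is read while an analgesic or physiotherapy is still working, and that therapy then stops. The baseline is too low relative to week 4, and the measured improvement is the response to trial treatment less the loss of the old therapy. A patient who arrived on nothing has no such offset. This heterogeneity enters the change score as noise, lowers mean improvement in each arm, and moves some patients below the responder thresholds. The article gives neither the share of patients on prior therapy nor the size of the loss.

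**Working it through.** **Inputs from the article.** Sample Size Calculation: 3.57 (SD 1.35) for Tuina with oil, 2.61 (SD 1.39) for Tuina with water, 50 per arm. Statistical Analysis: two-sided α = .05. The pilot values are treated here as VAS changes, since the stated target is a difference in change.

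**Assumptions.** A share f of patients in each arm stops a prior therapy and loses w VAS points of measured improvement. The worked case is f = 0.40 and w = 1.0 to 1.5. The wider range is f = 0.2 to 0.5 and w = 0.5 to 2.

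**1. The plan's own figures.** Pooled SD = √((1.35² + 1.39²)/2) = 1.37, and d = 0.96/1.37 = 0.70, as stated. With 50 per arm, SE = 1.37 × √(2/50) = 0.274. Two-sided power ≈ Φ(0.96/0.274 − 1.96) = Φ(1.54) = 0.94, or 0.93 by the t distribution, before dropout.

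**2. Is the primary contrast biased?** The expected offset is f × w in both arms and cancels in the difference. In simulations of 50 per arm (4,000 runs per scenario) over the wider range, the unadjusted difference averaged 0.95 to 0.97 against a true 0.96.

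**3. Added variance.** SD of change = √(1.37² + f(1 − f)w²).

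| | No prior-therapy loss | f = 0.40, w = 1.0 | f = 0.40, w = 1.5 |
|---|---|---|---|
| SD of change | 1.37 | √(1.877 + 0.24) = 1.46 | √(1.877 + 0.54) = 1.56 |
| 95% half-width, 1.96 × SD × √(2/50) | 0.54 | 0.57 | 0.61 |
| Power (t) | 0.93 | 0.90 | 0.86 |

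The normal approximation gives 0.94, 0.91 and 0.87. Over the wider range, power runs from about 0.93 down to 0.80, and adjusting for prior therapy brings it back to about 0.93.

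**4. Chance imbalance.** The SE of the between-arm difference in prior use is √(2 × 0.4 × 0.6/50) = 0.098, so its 95% range is ±0.19. Multiplied by w, this is ±0.19 to ±0.29 VAS points, or 20% to 30% of 0.96. It is already part of the wider intervals in step 3 and is not an additional error.

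**5. Within-arm change.** It is understated by f × w = 0.4 to 0.6 points.

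**6. Responders (VAS reduction of at least 2).**
- No loss: Φ((3.57 − 2)/1.35) = 88% and Φ((2.61 − 2)/1.39) = 67%; risk ratio 1.31.
- Affected patients, w = 1.0: Φ(0.57/1.35) = 66% and Φ(−0.39/1.39) = 39%. Mixed 60:40 with the unaffected: 79% and 56%; risk ratio 1.42.
- Affected patients, w = 1.5: Φ(0.07/1.35) = 52% and Φ(−0.89/1.39) = 26%. Mixed 60:40: 73% and 51%; risk ratio 1.45.

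The risk ratio moves in expectation because a common downward shift does not cancel in a ratio.

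**7. Form of the adjustment.** Baseline is a response in the stated model. A main effect of prior treatment moves all five visits equally, so with complete data it leaves the change from baseline, and hence the group-by-time estimate, as it was. Only the interaction with time removes the offset. At f = 0.40 and w = 1.5, adjusting the change score for prior therapy, which is equivalent, reduced the simulated SD of the estimate from 0.31 to 0.28.

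**The case against.** The strongest reply is randomization. Both arms enter and stop therapies under one rule, and the primary estimand is a between-group difference, so earlier therapy does not confound it. That stands fully. A reader might infer from the missing washout that the oil effect itself is mixed with withdrawal of earlier treatment. That is true of each arm's change, but not of the contrast.

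Second, the order of events is inferred. The article does not say that VAS or JOA is read before other therapies stop, and it gives no figure for prior use. This also stands, and it makes every size above conditional.

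Third, chance imbalance is ordinary random error that the standard error captures, and other unadjusted prognostic factors act in the same way. This is correct. The case for adjustment is that this factor is already recorded, and recorded for this stated purpose.

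Fourth, the covariate list is introduced as what the covariates include, so it may not be exhaustive, and an analysis plan that is not shown may use the record. This stands in part. However, the article does fix the model terms and name five covariates, and it omits the one variable that it presents as its safeguard.

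A reader might also see a contradiction with Infrared Thermal Imaging, where the subject "shall not take any medication that affects body temperature orally within 24 hours" and has no physical therapy. That is a preparation condition for one test. It can hold alongside the absence of a formal washout before enrollment, so it is no conflict.

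**Conclusion.** The point holds as one of precision and interpretation. The primary between-group difference is unbiased in expectation (0.95 to 0.97 simulated against 0.96). What remains depends on how many patients came on active therapy and how much they lost by stopping.

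- **Primary test:** with 40% losing 1.0 to 1.5 points, about 3 to 7 percentage points of power are lost. Over the wider assumed range the loss is from nearly none to about 13 points. Adjustment recovers nearly all of it.
- **Responders:** proportions fall in both arms and the VAS risk ratio moves from about 1.31 to 1.42 to 1.45, with the pilot values read as normally distributed changes. The JOA responder result is open to the same shift, but the article gives no JOA figures to size it.
- **Within-arm change:** understated by 0.4 to 0.6 points in the worked case.

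If few patients were on prior therapy, or if baseline was in fact read after it stopped, the effect is negligible.

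**What to change.** Before the formal analysis, which the article says has not begun:

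1. Add recorded prior treatment at baseline and its interaction with time to the VAS and JOA mixed models. State that the interaction is required, because adding the variable to the covariate list as a main effect would not help.
2. Add prior treatment as a covariate in the VAS and JOA responder models.
3. Add a sensitivity analysis restricted to patients with no prior treatment, reported as an estimate with its interval. At the assumed 40%, about 60 of the 100 patients would remain, so its power is limited.
4. Report prior treatment by arm, and state that within-arm change and arm-level responder rates are not to be read as treatment effects.

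The data are already collected. Coded as any or none, the adjustment takes five parameters per mixed model (one main effect and four interaction terms with five visits). No change to conduct is needed: all 100 participants are reported as enrolled, and no washout rule is proposed.

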### Randomization and Allocation Concealment

Using SPSS (version 27.0; IBM Corp) for Windows software, a random number table was generated and randomly grouped into 2 sets in order of enrollment: the observation group, treated with a combination of Tuina and medicated oil; and the control group received the same Tuina technique, but the activating oil was changed to water, forming a control group with the treatment group.

### Blinding

Due to the nature of manual therapy combined with topical application, complete blinding of all parties is inherently challenging. Several measures were implemented to maximize blinding feasibility. They were the following: (1) participants neither handled nor observed the bottles during treatment, and allocation will be concealed from all the participants; (2) the patients will be informed that they will receive one of two effective interventions, which will be randomly assigned after enrollment; (3) this study’s coordinator will notify participants of the randomized results and schedule any necessary interventions; (4) the group allocation will be kept concealed from data managers, statisticians, and evaluators throughout the procedure to minimize bias; (5) medicated oil and water are packed in bottles of the same shape, size, and color, and the bottles are encoded according to a random sequence; and (6) the bottle cap of water is soaked in activating oil to replicate its odor. In practical Tuina applications, apart from its odor, the medicated oil used in this study exhibits physical properties comparable to those of water, including fluidity, spreadability, viscosity, and skin contact characteristics. The Tuina practitioner and the cutaneous sensation experienced by participants during manipulation are broadly similar between the 2 intervention media in handling properties, which reduces the likelihood that therapists can reliably distinguish group allocation during treatment based on touch alone, thereby further limiting potential operator-expectation bias.

### Observation Group (TNO Group)

The dedicated attending physician of the Tuina Department is responsible for the treatment of Tuina. Tuina doctors have graduated from the Tuina College of Shanghai University of TCM, majoring in acupuncture, moxibustion, and Tuina, and have been occupied with clinical Tuina work for 5‐8 years. We finished standardized training on the techniques before treatment begins and ensured patients are treated only after passing the assessment. According to the diagnostic and treatment standards, the Tuina techniques established by the expert group will be used for intervention. The specific plan is as follows:

Rubbing tendons is applied to the paraspinal erector spinae muscle of the lumbar spine using the palm root kneading method. Up and down reciprocating operation is performed in 3 minutes. Apply, in 3 minutes, the thumb Tuina method to the attachment area of the iliac crest muscle, the affected buttocks, popliteal fossa, and calf, focusing on the areas where the patient feels sore and swollen.Apply the thumb folding finger flicking technique to the lumbar quadratus muscle, transverse process of the third lumbar vertebra, and Ashi acupoint (tenderness point or local cord-like or nodular area), with 3‐5 flicks per area, reaching the affected area. To loosen adhesions and relieve spasms for 2 minutes.Grab the affected buttocks and calf muscles for 2 minutes.The patient is advised to take a standing position and perform extreme movements such as waist flexion, lateral flexion to the left and right, and forward flexion to the left and right for 2 minutes. This is to stretch the muscles in the lower back.The patient is prone when using medicated oil for external rubbing. According to the instructions, take 8‐10 drops of the medicated oil. First, apply the medicated oil evenly to the affected area using the palm-rubbing method, and then take 6‐8 drops of the medicated oil. Use the palm rubbing method to horizontally rub the lumbar and sacral areas and vertically rub the Du meridian and foot sun meridian tendons, each about 5‐7 times, with a degree of heat transmission. At the pain point, use techniques combined with activating meridian oil to perform Tuina and pluck for 8 minutes.

The treatment frequency is 3 times a week, for 20 minutes each time.

The treatment cycle is for 4 weeks, with a total of 12 treatments. The specific action characteristics are shown in Figures 3A-3E.

**Figure 3. F3:**
[figure not shown]
(A) Lumbar flexion, (B) left lumbar flexion, (C) right lumbar flexion, (D) left anterior lumbar flexion, and (E) right anterior lumbar flexion.

### Medicated Oil Drug Information

The brand was FEMO (executive standard number: JZ2017004).

The product registration number was ZC20170003, with a specification of 50 mL.

The medicinal ingredients were *P notoginseng* (Burk) F.H. Chen, *A carmichaelii* Debx., *A erubescens* (Wall.) Schott, *P ternata* (Thunb.) Breit, *C tinctorius* L., methyl salicylate (wintergreen oil), menthol, camphor, eucalyptus oil, lavender oil, rose oil, and olive oil.

FEMO is a government-approved proprietary Chinese medicine manufactured under good manufacturing practice standards. The alkaloids from *A carmichaelii* are strictly controlled during processing to ensure compliance with safety requirements. The product is approved for external use and has been lawfully marketed in Hong Kong (registration number: HKC-00369).

### Control Group (TNW Group)

Using the Tuina technique in the above plan, we performed step 5. When we applied the medicated oil externally, we replaced the medicated oil with clean water to form a control.

The treatment frequency was 3 times a week, for 20 minutes each time. The treatment cycle was 4 weeks.

### Outcome Measurement

Through the combination of VAS, Japanese Orthopaedic Association scores (JOA), tenderness score, infrared thermal imaging, and muscle tension testing, this study comprehensively evaluates the effectiveness of the intervention, gathering both subjective (patient-reported) and objective (physiological) outcomes. The primary end point is the change in VAS score from baseline to week 4 (end of treatment). VAS is assessed at baseline and weeks 1, 2, 4, and 8; however, the week 4 assessment serves as the prespecified primary analysis time point.

### Primary Outcome

The VAS scoring standard, also known as the pain level scoring system, is a visual analog scale method used to evaluate the severity of pain. A 10-cm-long straight line is used, with both ends representing 0 points for painless and 10 points for extreme pain. The scale is: 0 is no pain, 1‐3 indicates mild pain, 4‐6 moderate pain, and 7‐10 severe pain. After introducing the key points, the patient will self-evaluate the degree of pain based on their feelings [32].

### Secondary Outcome Measurements

#### About JOA

The JOA scale evaluates both subjective symptoms and objective signs. The total score of the scale is 29 points, assessed across 5 aspects and 25 items [33]. The score is directly proportional to the function. The larger the scale score, the milder the subjects’ symptoms.

#### Infrared Thermal Imaging

Using infrared thermal imaging (FLIR ONE Pro, FLIR Systems, Inc) measurement method: maintain indoor temperature at 26 ℃±2 ℃, humidity at 45%-60%, maintain stable indoor air without convection, and avoid direct wind blowing to the examination site or between the subject and the camera. The subject shall not take any medication that affects body temperature orally within 24 hours, shall not undergo physical therapy, and shall not drink alcohol. The subject should lie prone, rest for a moment, maintain a certain balance in body temperature, wait for the skin to dry and become sweat-free, and then expose the tested area for 5 minutes before taking photos. The corresponding colors on the infrared image from high temperature to low temperature are white, deep red, red, light red, yellow, green, light green, light blue, deep blue, and black. Identify the pain points in the patient’s area and mark them accordingly. Measure the temperature of the pain points in the pain area before enrollment, at week 1, at week 2, and after week 4 of treatment. The location of the pain points in the pain area is determined based on palpation, patient feedback, and the first infrared thermography image. A low temperature in the pain area before treatment indicates poor local blood circulation and a decreased pain threshold. A high temperature at pain points after treatment indicates good local blood circulation and an increased pain threshold. The testing unit we used was ℃.

